### Implementation

An unblinded member of the research team (e.g. project manager, research midwife) will input the participant’s ID number and study site into the online Sealed Envelope system. The system sends the random group allocation via email to the unblinded team member, who will inform the participant of their allocated study group and arrange the app onboarding session if applicable.

#### Blinding

The trial statistician and the research assistant conducting all follow-up assessments will be blinded to treatment allocation. The circumstances around any un-blindings will be recorded and discussed. Other research team members (e.g. project manager, research midwife) will not be blinded to treatment allocation as they will conduct study procedures requiring knowledge of participants’ treatment allocation (e.g. app setup, monitoring app responses). It will also not be possible to blind participants to the group of allocation.

### Intervention and control groups

#### Usual care plus digital screening

Participants in the digital screening group will be asked to use the CareLoop PND app from study entry until 8 weeks postpartum, in addition to their usual NHS care. This specific intervention end date was selected to enable a fair comparison with usual care: within UK health services, at 6–8 weeks postpartum, mothers should be offered a health check, including mental health screening questions [32]. Research midwives will instruct participants in how to download, configure and use the app, with the help of an instructional video. Participants without a suitable smartphone will be lent a study phone until 8 weeks postpartum. All participants will be offered £10 phone credit per month that they are using the app, up to £30 in total.

The app contains additional features, such as a graph of the user’s responses to the daily questions over time, randomly selected daily inspirational quotes, a diary for the user to keep their own daily notes about their mental health (not uploaded), phone numbers of local and national mental health helplines, and links to external resources with information about parenting and baby health. Research midwives will phone participants 1, 2, 4, and 8 weeks after randomisation to check for adverse events (reported in the study’s adverse events form) and/or technical issues (referred to the technical team). The timing of these phone calls has been chosen to roughly mirror the timing of antenatal and postnatal midwife/health visitor appointments in standard care.

#### Usual care alone

Participants allocated to this group will continue with their usual NHS care, which typically includes some mental health screening as part of usual midwife and health visitor appointments (not standardised).

### Outcomes

#### Primary outcome: feasibility

The primary objective of the study is to evaluate feasibility of delivering a full-scale, single-blind, RCT within NHS services. In this feasibility trial, the a priori criteria for considering a full-scale RCT to be feasible are:i.App engagement: overall completion rate of > 33% of daily app assessments AND > 50% of participants complete > 50% app-based EPDS assessments.ii.Retention: > 80% participants retained at 8 weeks postpartum OR > 80% participants retained at 6 months postpartum.iii.Data completeness: > 80% availability of relevant participant electronic health records (midwife, GP and health visitor electronic health records from baseline to 8 weeks postpartum) OR > 80% completion of the Mini International Neuropsychiatric Interview (MINI) at 6 months postpartum.

#### Justification of feasibility criteria

The first clause of the app engagement feasibility criterion (> 33% usage) is a threshold that is widely used in digital health studies to indicate sufficient app engagement, having originated in the Ecological Momentary Assessment literature [33]. In the current study, a participant meeting this threshold would answer app-based EPDS questions every three days, on average, providing plenty of mental health screening information (far more than is gathered in standard care). The second clause of the app engagement criterion (> 50% participants completing > 50% app assessments) was added to further strengthen the criterion by ensuring that usage was distributed across the sample rather than skewed towards a small number of high engagers.

Feasibility criteria ii and iii (retention and data completeness) each have two clauses, connected by ‘OR’. Two options are needed in each case because the primary outcome of the future full-scale RCT has not yet been decided. A secondary objective of the current feasibility trial is to examine suitability of two specific candidate primary outcomes for a full-scale RCT: (a) number of true positive and false positive screens identified by usual care (reported in electronic health records) between baseline and 8 weeks postpartum compared to those identified by digital screening in the same period, and (b) mental health status at 6 months postpartum (measured using the MINI). Depending on which primary outcome for the full-scale trial is chosen (a or b), retention at 8 weeks postpartum (for a) or 6 months postpartum (for b) is most relevant for feasibility criterion ii. Similarly, for feasibility criterion iii, availability of electronic health records (for a) or completion of MINI at 6 months postpartum (for b) would be most relevant. Hence, within the current feasibility RCT, it is necessary to examine retention at both timepoints and data completeness of two outcomes.

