**Methods:**

In this single-blind randomised feasibility trial, participants (*n* = 80) will be recruited during late pregnancy from two NHS maternity services and randomised (1:1) to receive CareLoop PND alongside their usual NHS care, or usual care alone. Those in the experimental arm will use the CareLoop PND app daily from ≥ 36 weeks’ pregnancy until 8 weeks postpartum. During this period, participants scoring above EPDS screening thresholds (via the app or standard care) will be assessed to confirm diagnosis. True positive PND cases identified by digital screening will be referred to services for support. A blinded researcher will conduct follow-up assessments using clinical and health economic measures at 8 weeks and 6 months postpartum. At 8 weeks postpartum, experimental arm participants will also provide qualitative and quantitative feedback exploring app usability, acceptability, and implementation. Feasibility of delivering a full-scale RCT will be evaluated using a priori criteria relating to app engagement, study retention and completion of candidate primary outcome measures.

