## Background

Perinatal mental health is a global mental health concern [1], with 1 in 5 women experiencing a change in their mental health during their pregnancy or within a year of giving birth [2]. Meta-analyses indicate that 17% of mothers develop postnatal depression (PND) during the year after their child’s birth [3, 4], with suicide the leading cause of direct maternal death from 6 weeks to 12 months postpartum [5]. Although diagnostically identical to depression at other times, the consequences and costs of PND are substantially greater due to adverse effects on infants as well as parents. PND can affect parental wellbeing, the parent-infant bond, the child’s development, and parents’ and children’s long-term physical and mental health [6, 7].

In England, the publicly funded health service (National Health Service; NHS) has identified increasing access to high quality perinatal mental health care as a key priority in its Long Term Plan [8]. For parents and their children, the lifelong consequences of not accessing such care are estimated to cost the NHS and social care £1.2 billion per 1-year birth cohort [9]. Although medication and talking therapy can be used to successfully treat PND, identifying who needs treatment is difficult. National reports [7, 9, 10] and our local audit data (unpublished) suggest that more than half of cases of PND currently go undetected and untreated. Our study seeks to improve detection of maternal PND, to allow appropriate referral to existing perinatal mental health services.

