#### Secondary outcomes

Table 1 outlines the five secondary objectives and their associated outcomes.

**Table 1 Tab1:** Secondary objectives and associated outcomes

	Objective	Outcome
1	To examine participant recruitment and identify barriers to recruitment	• The proportion of eligible individuals agreeing to participate • Reasons for declining to participate
2	To examine the suitability of two candidate primary outcomes for a full-scale trial	The extent and pattern of missing data, presence of floor/ceiling effects, and variability in responses in: a) number of true positive and false positive screens identified by usual care and digital screening between baseline and 8 weeks postpartum b) MINI at 6 months postpartum
3	To examine the suitability of other proposed clinical measures and health economic measures	The extent and pattern of missing data, presence of floor/ceiling effects, and variability in responses in: • PHQ-9 (baseline and after positive screen) • GAD-7 (baseline and after positive screen) • MINI (8 weeks) • Postpartum Bonding Questionnaire (8 weeks, 6 months) • Healthcare Resource Use Questionnaire (baseline, 8 weeks, 6 months) • EQ-5D-5L (baseline, 8 weeks, 6 months)
4	To examine the acceptability and usability of the digital screening system and participants’ experiences of using it	Qualitative (interview) and quantitative (MARS) data from participants in the app use group regarding app acceptability, usability, and experiences of using the digital screening system
5	To examine the safety of the digital monitoring system and study procedures	The number of adverse events (AEs) and serious adverse events (SAEs) and whether they are judged to be related to the app or other study procedures

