#### Tertiary outcomes

Summary statistics for the two candidate primary outcomes for a full-scale trial:The number of true positive and false positive screens identified by usual care and digital screening between baseline and 8 weeks postpartum. True positives are defined as cases scoring above EPDS screening threshold (usual care threshold: total EPDS score ≥ 12; digital screening threshold: total EPDS ≥ 12 on three consecutive reports) and scoring ≥ 10 on PHQ-9 or GAD-7 in a subsequent assessment by a blinded researcher. False positives are cases scoring above EPDS screening threshold but scoring < 10 on PHQ-9 and GAD-7.MINI score at 6 months postpartum.Summary statistics for the other clinical outcomes (MINI, Postpartum Bonding Questionnaire) and health economic outcomes (Healthcare Resource Use Questionnaire, EQ-5D-5L) at 8 weeks postpartum and 6 months postpartum.Key drivers of cost identified by the Healthcare Resource Use Questionnaire.

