#### Blinded follow up assessments: 8 weeks and 6 months postpartum (both groups)

At 8 weeks and 6 months postpartum, a blinded researcher will assess all participants using the MINI, a short, structured diagnostic interview for DSM-IV and ICD- 10 psychiatric diagnoses [35]. Three relevant subscales of the MINI will be used in this study: major depression (subscale A), suicidality (subscale B) and generalised anxiety disorder (subscale N). Participants will also be assessed with three self-report measures during each follow-up assessment: a generic health status questionnaire (EQ-5D-5L), a bespoke questionnaire assessing health and social care resource use during the follow up period (unpublished), and a validated questionnaire assessing parental bonding with their baby (Postpartum Bonding Questionnaire) [36]. Regarding choice of assessment timepoints, the 8-week postpartum assessment aligns with the end of the intervention period. The 6-month postpartum assessment point was chosen to allow time for screening (digital screening or usual care screening) to have an effect on participants’ mental health. Specifically, time will be needed for participants screening positive for PND to be referred for additional mental health care (e.g. talking therapy, medication) and for that care to take effect.

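### Candidate outcome (a) is worded by screening route and counts only verified screen-positives, including anxiety-only cases, so it gives no share of PND detected; restate it by arm and set it against the 8-week MINI

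*Protocol article*

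**What the plan says.** The protocol article (Justification of feasibility criteria) gives candidate outcome (a) as the "number of true positive and false positive screens identified by usual care (reported in electronic health records") between baseline and 8 weeks, "compared to those identified by digital screening in the same period". Table 1 and the Tertiary outcomes list under Outcomes repeat the wording by route.

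On case definition, Tertiary outcomes states: "True positives are defined as cases scoring above EPDS screening threshold", with confirmation by "scoring ≥ 10 on PHQ-9 or GAD-7 in a subsequent assessment by a blinded researcher". The same either-or rule appears in the description of the digital arm and in Case note review. The abstract gives these cases a depression label: "True positive PND cases identified by digital screening will be referred to services for support". The explanation of the geographical restriction under Eligibility criteria also calls them PND screens.

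On verification, Table 1 lists "PHQ-9 (baseline and after positive screen") and does the same for GAD-7. After baseline, therefore, women who never screen positive are not assessed with either instrument. Separately, "At 8 weeks and 6 months postpartum, a blinded researcher will assess all participants using the MINI", with major depression and generalised anxiety as separate modules. Table 1 places the 8-week MINI among the other clinical measures, and the article does not link it to screen result.

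The Background says that "more than half of cases of PND currently go undetected and untreated" and that the study seeks to improve detection.

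**The concern.** Examining whether (a) suits a full trial is a named secondary objective. Table 1 judges this on missing data, floor or ceiling effects and variability. An outcome could pass all three and still not tell the team what it needs to know about detection. Three features of the definition cause this.

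- **Contrast.** A woman in the digital arm found through her health visitor is credited to usual care, and a woman found by both routes appears under both. The randomised question is whether adding digital screening to usual care finds more women.
- **Missed cases.** Only true and false positives are defined, so the share of PND that each arm detects is not available from (a).
- **Target condition.** A woman with GAD-7 of 10 or more and PHQ-9 below 10 is a true positive in a trial of depression detection.

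At stake is the choice of primary outcome for the full trial, not the feasibility result of this one.

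**Working it through.** **The plan's own figure.** The article gives no figure for outcome (a). Its only precision figure is ±11% for attrition with n = 80 (Sample size). With half-width 1.96 × √(p(1−p)/n), p = 0.5 and n = 80, this is 1.96 × √(0.25/80) = 0.1096, so it reproduces. That assumes a 95% interval and p = 0.5, neither of which is stated. It applies to a proportion of all 80 women and does not carry over to a proportion among depressed women.

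**Route against arm.** The digital arm uses the app in addition to usual NHS care (Usual care plus digital screening). Records are reviewed for usual-care EPDS scores in both groups (Case note review). Data are analysed by allocated arm (Data analysis). Usual-care screens therefore arise in both arms, and a contrast by route is not a contrast by arm.

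**What a count of true positives leaves open.** Share detected = TP / (TP + missed). With TP = 3 in an arm (illustrative):

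| Missed | Share detected |
|---|---|
| 0 | 3/3 = 100% |
| 1 | 3/4 = 75% |
| 3 | 3/6 = 50% |
| 6 | 3/9 = 33% |

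Outcome (a) is the same in all four rows.

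**Effect of the either-or rule.** Take 7 PND cases and 5 counted true positives (illustrative). The apparent share is 5/7 = 71%. If 1, 2 or 3 of the 5 are GAD-7-only, the share of PND detected is 4/7 = 57%, 3/7 = 43% or 2/7 = 29%.

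**What (a) can still give.** Let π be the proportion of women with PND, equal in expectation between arms by randomisation, and s the share detected in an arm. Verified depression true positives per randomised woman are then π × s, and the ratio between arms is s(digital) / s(usual). Relative detection can be estimated without counting missed cases, provided the count is by arm and depression-specific. The absolute share cannot.

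**What the 8-week MINI adds, and its limit.** In each arm let D be MINI depression cases with any positive screen and M those with none. Let E be women who are MINI-negative at 8 weeks but had a positive screen confirmed by PHQ-9 ≥ 10.

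- MINI-only share: D / (D + M).
- Extended share: (D + E) / (D + M + E).

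The MINI is given once, at the end of the screening window. A case detected early and resolved by 8 weeks drops out of the first share, possibly more often in one arm. The second share restores those cases, but not undetected cases that resolved. Because E enters both its numerator and its denominator, it is never below the first. Neither is definitive, so both should be shown.

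**Precision.** With about 40 women per arm (80 allocated 1:1), an assumed 8-week prevalence of 5% to 20% gives 40 × 0.05 = 2 to 40 × 0.20 = 8 cases per arm. The article's 17% is a one-year figure; it gives 40 × 0.17 = 6.8, or 5.4 with 80% retained. Exact 95% intervals: 1 of 2 detected, 1% to 99%; 4 of 7 (57%), 18% to 90%; 4 of 8 (50%), 16% to 84%.

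**The case against.** **The layout could be left to the analysis plan.** Data analysis says participants are analysed by allocated arm, and clinical measures are to be summarised by group, so arm tables are available. This stands in part. However, the article itself fixes the definition of (a), its true-positive rule and the criteria for judging it, and that definition is by route.

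**Randomisation removes the need to count missed cases.** For a comparative trial, true positives per randomised woman by arm are enough to estimate relative detection. This stands. A reader might infer that (a) cannot be judged suitable at all, and the documents do not support that. Candidate (b), the MINI at 6 months, also reflects the consequences of missed cases in everyone.

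**The either-or rule is deliberate.** It is stated consistently, matches the entry exclusions and still requires a positive EPDS. This stands as far as the rule goes. What remains is the PND label and the missing breakdown.

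**Stronger readings that do not hold.** The word screens might suggest that daily reporting lets one woman be counted many times. Case note review counts participants and Tertiary outcomes counts cases, and nothing counts successive runs of reports separately. A reader might also infer that the two counts rest on denominators of different size because usual care reaches both arms. That requires pooling by route across arms, which no section states and the by-arm analysis does not support. That a digital referral prompts a health-visitor EPDS is plausible, but the article says only that symptom information is sent.

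**Conclusion.** The point holds as a low-cost improvement to a stated definition. As written, (a) contrasts routes, verifies only screen-positives and includes anxiety-only positives under a PND label. It therefore gives neither missed cases nor the share of PND detected, although missed cases are the article's stated rationale. The 8-week MINI, collected blind in both arms, can supply most of what is missing for depression present at 8 weeks, but not for cases that resolved earlier.

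The size is that of an information gap, not a bias in a reported result: the same count fits shares from 33% to 100% in the illustration. The added measure would be very imprecise, at about 2 to 8 cases per arm under an assumed prevalence of 5% to 20%. Women with PHQ-9 or GAD-7 of 10 or more are excluded at entry, so the lower part of that range is plausible. The trial can show that the measure works in practice and can describe it, but cannot estimate it well. The primary feasibility criteria do not depend on these counts, and no between-arm tests are planned.

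**What to change.** 1. Define (a) per randomised woman and by randomised arm: at least one verified true positive by any route (yes or no). Define false positives in the same way, and give route as a breakdown within arm.
2. Report PHQ-9 ≥ 10 separately from GAD-7-only positives, and reserve the PND label for the former.
3. As part of judging whether (a) is suitable, cross-tabulate any positive screen (either route) against blinded 8-week MINI major depression by arm, with exact intervals and the number lacking a MINI.
4. Show the share detected on both denominators: MINI depression cases alone, and MINI depression cases plus screen-positive cases confirmed by PHQ-9 ≥ 10. State that cases resolved before 8 weeks may be MINI-negative, possibly differently by arm, and label the result descriptive.

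The cost is a revised definition and a few tables. All the data are already to be collected, and assessments, sample size and feasibility criteria do not change.

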#### Secondary outcomes

Table 1 outlines the five secondary objectives and their associated outcomes.

**Table 1 Tab1:** Secondary objectives and associated outcomes

	Objective	Outcome
1	To examine participant recruitment and identify barriers to recruitment	• The proportion of eligible individuals agreeing to participate • Reasons for declining to participate
2	To examine the suitability of two candidate primary outcomes for a full-scale trial	The extent and pattern of missing data, presence of floor/ceiling effects, and variability in responses in: a) number of true positive and false positive screens identified by usual care and digital screening between baseline and 8 weeks postpartum b) MINI at 6 months postpartum
3	To examine the suitability of other proposed clinical measures and health economic measures	The extent and pattern of missing data, presence of floor/ceiling effects, and variability in responses in: • PHQ-9 (baseline and after positive screen) • GAD-7 (baseline and after positive screen) • MINI (8 weeks) • Postpartum Bonding Questionnaire (8 weeks, 6 months) • Healthcare Resource Use Questionnaire (baseline, 8 weeks, 6 months) • EQ-5D-5L (baseline, 8 weeks, 6 months)
4	To examine the acceptability and usability of the digital screening system and participants’ experiences of using it	Qualitative (interview) and quantitative (MARS) data from participants in the app use group regarding app acceptability, usability, and experiences of using the digital screening system
5	To examine the safety of the digital monitoring system and study procedures	The number of adverse events (AEs) and serious adverse events (SAEs) and whether they are judged to be related to the app or other study procedures

#### Tertiary outcomes

Summary statistics for the two candidate primary outcomes for a full-scale trial:The number of true positive and false positive screens identified by usual care and digital screening between baseline and 8 weeks postpartum. True positives are defined as cases scoring above EPDS screening threshold (usual care threshold: total EPDS score ≥ 12; digital screening threshold: total EPDS ≥ 12 on three consecutive reports) and scoring ≥ 10 on PHQ-9 or GAD-7 in a subsequent assessment by a blinded researcher. False positives are cases scoring above EPDS screening threshold but scoring < 10 on PHQ-9 and GAD-7.MINI score at 6 months postpartum.Summary statistics for the other clinical outcomes (MINI, Postpartum Bonding Questionnaire) and health economic outcomes (Healthcare Resource Use Questionnaire, EQ-5D-5L) at 8 weeks postpartum and 6 months postpartum.Key drivers of cost identified by the Healthcare Resource Use Questionnaire.

